## Abstract

**Background:**

Family-based treatment (FBT) is an efficacious outpatient intervention for young people diagnosed with Anorexia Nervosa (AN). To date, treatment to protocol has relied on standard face-to-face delivery. Face-to-face therapy is subject to geographic, temporal and human factors, rendering it particularly susceptible to inequities and disruption. This has resulted in poorer service provision for rural and regional families, and recently a significant challenge to providing face-to-face services during the COVID-19 global pandemic. The present study examines whether FBT for AN can be successfully translated to a digital delivery platform to address these access issues.

**Method:**

Forty young people aged 12 to 18 years who meet DSM-5 diagnostic criteria for AN, and live in a rural or regional setting, will along with their family be recruited to the study. Trained therapists will provide 18 sessions of FBT over 9 months via telemedicine to the home of the young person and their family. The analysis will examine treatment effectiveness, feasibility, acceptability, and cost-effectiveness.

**Discussion:**

The study addresses the treatment needs of families not able to attend face-to-face clinical services for evidence-based treatment for eating disorders. This might be due to several barriers, including a lack of local services or long travel distances to services. There has been a recent and unprecedented demand for telemedicine to facilitate the continuity of care during COVID-19 despite geographical circumstances. If delivering treatment in this modality is clinically and economically effective and feasible, it will facilitate access to potentially lifesaving, evidence-based treatments for families formerly unable to access such care and provide evidence for the continuity of services when and where face-to-face treatment is not feasible.

## Background

Anorexia nervosa (AN) is a serious psychiatric disorder, with numerous negative physical and psychological health impacts [1–3]. It is the third most common chronic disorder affecting adolescent girls [4], although AN affects both genders and is present across the entire lifespan [5]. Children and adolescents are especially vulnerable to the physical consequences of AN such as stunted growth, poor bone health, cardiac complications, infertility, and changes to brain structure [6]. The average duration of AN is 5 to 7 years [7], although long-term follow-up evidence suggests that after a 10-year duration of illness, only 30% of individuals are recovered [8]. Individuals diagnosed with AN have approximately 12 times greater risk of death, and a 57 times greater risk of suicide compared to same-age peers [2]. Given the seriousness of the disorder, treatment must be delivered efficiently and effectively.

Currently, Family-Based Treatment (FBT) is the most efficacious therapy for adolescents with AN [9–11] recommended by international clinical practice guidelines [12, 13]. FBT has been manualised as a face-to-face outpatient behavioural intervention and emphasises parental support as the primary resource in the recovery of adolescents with AN [14]. Several randomised controlled trials (RCTs) have demonstrated the efficacy of FBT for adolescent AN [10, 15–20]. Remission rates are particularly promising for adolescents with short illness duration [11, 16, 21]. The average remission rate for all participants at the end of FBT is approximately 40% [11, 22, 23]. An average of 75% of young people demonstrate improvement in weight and eating-related symptomatology at end of FBT [16].

There is a concerning inequity in access to eating disorder care for regional and rural populations. The implementation of specialised treatments, such as FBT, is challenged by several factors unique to the rural setting in New South Wales (NSW), Australia, a state with a population spread across a large geographic area. Rural health districts range from 11,335 km^2^ (kms) to 246,676 square kms with a population density that varies between .05 square km per person to .89 square km per person. Regional and rural areas are limited by a lack of support resources (such as support groups, consumer advocacy groups), and a limited number of trained professionals confident in the assessment, diagnosis, and treatment of AN [24, 25], particularly using FBT. Further, stigma and concomitant treatment avoidance are amplified by social visibility in small rural communities [26].

There are additional circumstances where available face-to-face treatment sessions are not feasible, such as co-occurring physical or mental health issues, difficulties with travel, families who live at a great distance from each other yet are required to attend sessions (as is the case in some separated families), or natural disasters, such as the recent Australian bushfires which severely impacted regional and rural areas. Furthermore, the recent COVID-19 pandemic forced the sudden shutdown of face-to-face services due to health risks and an anticipated increase in demand for inpatient services [27, 28]. Thus, rapid transition and adoption of new service delivery modalities are urgently required. There is an imperative need to demonstrate how evidence-based therapies, such as FBT, can be successfully delivered over digital platforms [29–31].

Technology, and specifically the use of telemedicine (or telehealth), appears to be an obvious solution [32]. The uptake of telemedicine in the treatment of eating disorders in regional and rural Australia before COVID-19 has been relatively slow [33], given the amount of research on the use of this mode of intervention for psychosocial treatment in other mental health diagnoses [34], such as adolescent ADHD [35] and post-traumatic stress disorder [36]. A systematic review demonstrated some positive findings for e-therapies in eating disorder treatment [37], and results from an RCT of Cognitive Behaviour Therapy-Enhanced (CBT-E) for Bulimia Nervosa (BN) delivered via telemedicine compared to face-to-face treatment demonstrate the need for further exploration of digital treatment delivery [38]. Further, a recent pilot study conducted in the USA found that FBT delivered via telemedicine is feasible, acceptable, and had equivalent outcomes to treatment delivered in traditional face-to-face therapy [14, 39, 40]. However, this pilot research involved a small sample size, treatment delivered was within a specialist eating disorder service, and with only one highly trained therapist. Consequently, little is known about the scalability and ‘real-world’ application of using telemedicine in the delivery of FBT. That is, within an already existing, non-specialist service, directly into the family home. Moreover, there is no evidence to date demonstrating the cost-effectiveness of FBT delivered using telemedicine compared with standard care (i.e. face-to-face care).

### Specific aims

The specific aims of the present study are to determine:
The effectiveness of FBT delivered via telemedicine in reducing core eating disorder symptomology, as well as general mood and anxiety, and improving quality of life to young persons with AN and their families living in regional and rural NSW, Australia;The feasibility and acceptability of using telemedicine into the home to deliver FBT to young persons with AN and their families; andThe economic costs and health consequences (clinical and quality of life outcomes) of using telemedicine to deliver FBT directly into the home.

## Method

### Overall study design

This is a four-year pre- and post-implementation study, with 2 years dedicated to treatment delivery, and up to 20 families per year, to reach a total sample size of 40 families. The study commenced in April 2020 (see Fig. 1 for the Study Timeline). The study protocol has been approved by a Human Research Ethics Review Board (HREC #2020/ETH00186).

**Fig. 1 Fig1:**
[figure not shown]
Study timeline for Family-based treatment for Anorexia Nervosa using Telemedicine (May 2020 – December 2023). Note: FBT = family-based treatment

### Setting

A secure online telemedicine platform will be used to connect the therapist located at the regional or rural mental health service to the family, who will be in their home.

### Participants

Young people, aged between 12 and 18 years who meet diagnostic criteria for AN as defined by the fifth edition of the *Diagnostic and Statistical Manual of Mental Disorders (DSM-5)* [41] will be recruited for this study. Given the importance of involving the whole family in treatment, the parents/guardians responsible for the young person’s recovery as well as siblings and any other family members involved in treatment will also be recruited. Participants will be a resident of a regional or rural health district in NSW, Australia. The reason for selecting regional and rural health districts is due to the already great need for specialist care in these regions given eating disorder services are sparse in usual service delivery circumstances. Primarily, participants will be recruited via the already existing referral pathways for mental health service for young people, such as via medical practitioners, schools, and local mental health services.

Three therapists from each of the five regional and rural health districts eligible for the study have been recruited (*n* = 15). Each therapist has the capacity to work with *n* = 2 families each year, with a maximum of *n* = 4 families during the study. The therapists providing treatment will contribute to the evaluation, and thus will be enrolled as participants. All therapists had to meet a minimum level of training and experience in FBT, obtain management support to enrol in the study, and commit to participate in additional training and regular supervision.

### Inclusion/exclusion criteria

The young person with AN must be medically stable for outpatient treatment verified by their medical professional [42]. The family must be committed to engaging in FBT, not be engaged in any other psychological or dietetic treatment for AN, have access to a computer or tablet device with videoconferencing functions, a reliable internet connection, access to a telephone or mobile phone if internet unavailable, and access to a reliable digital weighing scale at home. The study can provide some of these requirements to families to ensure equity of inclusion. Young people who require inpatient treatment for a physical or psychiatric illness, are dependent on alcohol or other substances, have acute suicidality, currently pregnant, or under compulsory treatment orders, are excluded from participating in this study.

### Videoconferencing platform

Picture and sound quality are of critical importance, and the investigators want to ensure technical issues do not compromise the therapeutic experience of the patient, family, and therapist. The videoconferencing platform facilitating treatment delivery has end-to-end encryption, integration with digital calendar platforms, password protection and can be used on any device. Video quality will depend on the speed of the family’s internet and the quality of their computer camera. In case the secure connection is lost or cannot be made, the therapist will attempt to reconnect via videoconferencing or call the family via phone.

### Therapist training

Therapists enrolled in the study will receive formal face-to-face training in FBT and using telemedicine from one of the investigators ([name]). [name] was senior author on the previously described USA pilot study [14, 39], has strong links to the training of FBT within Australia [10, 43], and co-authored the FBT treatment manual, *Treatment Manual for Anorexia Nervosa: A Family-based Approach* [44]. Training topics include advanced FBT skills, running the family meal session via videoconferencing, session structure and phases of therapy.

When the treatment delivery phase commences, the therapists will receive weekly group supervision with [name]. The supervision group will take place online using a videoconferencing platform. Focus areas of the consultation group will be largely dependent on the treatment progress of the therapists’ cases; however, likely topics will include treatment adherence, advanced FBT skills, moving through the phases of FBT, and managing therapeutic processes via telemedicine.

### Intervention

Eighteen sessions of FBT will be delivered over 9 months, as described in Lock and [name] [44], via telemedicine, to young people with a diagnosis of AN and their families. The key difference to standard FBT is the delivery modality, being video conferencing, and treatment setting, being directly into the family home, rather than face-to-face within the service. The young person’s medical and psychiatric health will be managed by their local general practitioner and/or psychiatrist.

After consent and before meeting with the therapist, a member of the research team will contact the family to perform a technology check, to troubleshoot any technology issues (i.e., video camera not working, teleconferencing platform issues or connection/speed issues), and offer education and training support concerning the videoconferencing platform. Before commencing therapy, the family will have a brief online session with the therapist. The purpose of this session is to orientate the family to the treatment format, describe the treatment process and discuss logistics that will enhance the therapy experience.

Before each scheduled session, the young person will be weighed using the same scales and in the same location of the house by the parent/guardian. As soon as the parents/guardians have measured the young person’s weight, they will send the weight to the therapist via email or text. As per the FBT manual [44], the young person will be weighed wearing light indoor clothing, no shoes and after voiding their bladder. The parents/guardians will be instructed by the therapist how to do this during the first session. The therapist will initiate the therapy session, and begin with an individual meeting with the young person [39, 44]. Following a review of the weekly weight and check in with the young person, the remaining family members will join the young person and therapist.

FBT comprises of three treatment phases [44, 45]. In phase 1, the parents are charged with the responsibility of managing eating behaviours and weight gain. In phase 2, parents gradually transition the responsibility of eating back to the adolescent in an age-appropriate manner. In phase 3, adolescent developmental issues (such as peer friendships or managing school/studies) become the focus of treatment. Due to the seriousness of AN, FBT requires all family members to attend sessions [44], and that appointments are at least weekly for the first several months [45]. This frequency of appointments generally reduces as the young person becomes progressively well [44].

### Fidelity

Treatment fidelity will be managed by therapists completing two workshops and weekly supervision with [name]. Furthermore, therapists will complete a brief checklist after each session and will use these to guide supervision discussions.

### Measures

Psychometric questionnaires will be utilised throughout treatment for research purposes and to monitor treatment progress. There will be several assessment points: baseline (T1), throughout treatment, mid-treatment (T2), end-of-treatment (T3), and at 6 months follow-up (T4) (see Table 1 for assessment schedule). In addition to psychometric questionnaires, the young person, parents/guardians and therapist will be invited to participate in a semi-structured interview at T3. The young person, parents/guardians, siblings/other family members and therapist will complete the assessments via a secure online data capture portal, REDCap. REDCap is a secure web application for building and managing online surveys and databases which is licenced to the University of Sydney. REDCap is compliant with just about any privacy and security standard – for example, HIPAA, Part-11, and FISMA standards (low, moderate, or high).

**Table 1 Tab1:** Assessment Battery and Schedule

	Baseline (T1)	Weekly (until T3)	Mid-Treatment (Session 9 (T2)	End of treatment (Session 18) (T3)	6-month Follow-up (T4)
*Demographics: age, gender, education, location etc*	X				
*Illness characteristics: duration, symptoms*	X				
*Wait time to commence FBT*	X				
*Resource use in HE: Hospital admissions (number and duration)*	X		X	X	X

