### Therapist

The therapist will note *Session attendance* of family members every session.

The *Therapist evaluation of feasibility and acceptability* will be measured using a brief online questionnaire and a semi-structured interview after treatment delivery for each family to explore the therapist’s experience of being in the study and delivering FBT via a telemedicine modality. In particular, the semi-structured interview will explore the therapist’s experience of utilising telemedicine to deliver FBT, what components of the alternate mode of delivery enhanced their clinical practice, what were the barriers and challenges, and suggestions and considerations for future implementation.

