### Data analysis

#### Aim 1: Effectiveness of delivering FBT via telemedicine

A mixed model logistic regression will be used to evaluate the effectiveness of FBT delivered via telemedicine, using change of %mBMI as the primary outcome from T1 to T3 and from T1 to T4. To determine the effectiveness, secondary analyses, again using a mixed model regression, will compare the young persons’ global EDE and EDE-Q, as well as the parents/guardians PEDE and PEDE-Q scores. Further, the young persons’ responses on the CIA, CET at T1, T2, T3 and T4 will be compared. The young persons’, parent/guardians, and sibling/other family members responses on the FAD and EQ-5D-5L/EQ-5D-Y in addition to the parent/guardian responses on the PVA will be analysed to determine changes in family functioning, parental efficacy, and wellbeing from T1 to T3 and T1 to T4.

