#### Aim 2: To determine the feasibility and acceptability of using telemedicine to deliver FBT

To examine the feasibility and acceptability of using telemedicine to deliver FBT we will utilise a mixed-method approach to analyse: (a) the number of patients/families that expressed interest in participating in the study; (b) the number of patients/families enrolled in the study (i.e., an indicator of treatment feasibility); (c) the number and percent of patients/families that completed at least 10 sessions (i.e., an indicator of treatment engagement); (d) the number of patients/families completing the full course of treatment (18 sessions; i.e., an indicator of treatment retention); (e) the results from the post-treatment evaluation survey and semi-structured interview by family members (i.e., family acceptability); (f) the results from the post-treatment evaluation survey and semi-structured interview by young people (i.e., young person acceptability); and (g) the results from the post-treatment evaluation survey and semi-structured interview by therapists (i.e., therapist acceptability).

A qualitative analysis will examine the participants’ responses to the semi-structured interviews that take place at T3. Given the lack of theory or framework regarding family acceptability and feasibility using telemedicine, a conventional content analysis method will be used [65]. The interviews will be analysed within and between participant roles (i.e., young persons, parents/guardians, siblings/other members and therapists) to determine what themes emerge that are similar across the groups, as well as those unique to each group. Two investigators (AH and [name]) with experience in qualitative research will immerse themselves in the data and allow for categories and names for categories to emerge from the data.

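### T2 and T3 are tied to session counts (9 and 18), so Table 1 gives families who stop before session 18 no defined T3, T4, evaluation survey or interview

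*Protocol article*

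**What the plan says.** In the Measures section, Table 1 heads two assessment columns by session number: "Mid-Treatment (Session 9 (T2" and "End of treatment (Session 18) (T3". T4 is a six-month follow-up whose starting point is not stated.

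The young person, parents and therapist "will be invited to participate in a semi-structured interview at T3", and the Aim 2 analysis again refers to "responses to the semi-structured interviews that take place at T3". Table 1 ticks the evaluation surveys at T3 only, for every participant group.

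The Aim 2 analysis includes "the number and percent of patients/families that completed at least 10 sessions (i.e., an indicator of treatment engagement", and as a separate indicator the number completing all 18 sessions.

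The Aim 1 analysis describes a mixed model logistic regression "using change of %mBMI as the primary outcome from T1 to T3 and from T1 to T4".

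The Intervention section plans 18 sessions over 9 months. It says that in FBT "appointments are at least weekly for the first several months", with appointments generally spaced out as the young person recovers.

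**The concern.** The assessment clock runs on sessions attended, and attendance is itself an outcome of the study. This has two consequences.

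First, a family that stops at, say, session 12 has no event in Table 1 that triggers T3. The same family has no clear origin for T4, and no trigger for the survey and interview, which exist only at T3. Families for whom home telemedicine did not work are plausible early leavers, and Aim 2 most needs to hear from them. No model can recover interviews and surveys that were never held.

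Second, session pace follows clinical response, so session 18 falls at different calendar times for different families. A T1-to-T3 change would then combine follow-up lengths that are related to the outcome, even among families who complete treatment.

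**Working it through.** **1. The plan's own figure.** Overall study design gives up to 20 families a year for 2 years: 20 × 2 = 40. This reproduces. The article gives no early-stopping rate.

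**2. What an early stopper contributes under Table 1, read literally.**
- Stops between sessions 9 and 18: has T1, T2 and the weights taken before each session attended. T3, T4, survey and interview are undefined.
- Stops before session 9: T2 is undefined too, so there is no post-baseline EDE, EDE-Q, CIA, RCADS or EQ-5D.
- Compulsive Exercise Test: Table 1 schedules it at T1, T3 and T4 only, so nobody has a post-baseline value before T3. (The Aim 1 analysis text also lists T2 for this scale, which Table 1 does not.)
- %mBMI: the Measures section collects weight before every session but height only at T1 to T4. Between those points %mBMI has to use an earlier height, and the weights end when the sessions end.

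**3. Calendar time of the session anchors.** Nine months is 9 × 52/12 = 39 weeks, with a midpoint of 19.5 weeks. How long weekly sessions last is an assumption, because the article says only several months.

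| Weekly phase (assumed) | Sessions used | Sessions left | Weeks left of 39 |
|---|---|---|---|
| 2 months (9 weeks) | 9 | 9 | 30 |
| 3 months (13 weeks) | 13 | 5 | 26 |
| 4 months (17 weeks) | 17 | 1 | 22 |

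In all three cases session 9 falls at about week 9, which is 9/39 = 23% of the planned course. A young person kept on weekly sessions throughout would reach session 18 at about week 18. One whose sessions are spaced out over the full course reaches it near week 39. If T4 is counted as 26 weeks from T3, it falls between week 18 + 26 = 44 and week 39 + 26 = 65.

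**4. Size if only families reaching session 18 were counted.** The Background gives an average remission rate of about 40% at the end of FBT, used here for illustration only: 0.40 × 40 = 16 of 40 (exact 95% interval 24.9% to 56.7%). Let m be the number stopping early and q their remission rate. Both are assumptions.

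Completer rate = (16 − q·m) / (40 − m)

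| Stop early | m | q = 40% | q = 20% | q = 0% |
|---|---|---|---|---|
| 10% | 4 | 40.0% | 15.2/36 = 42.2% | 16/36 = 44.4% |
| 20% | 8 | 40.0% | 14.4/32 = 45.0% | 16/32 = 50.0% |
| 30% | 12 | 11.2/28 = 40.0% | 13.6/28 = 48.6% | 16/28 = 57.1% |
| 40% | 16 | 40.0% | 12.8/24 = 53.3% | 16/24 = 66.7% |

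The excess over 40% is therefore 0 to 17.1 points at 30% stopping, and zero whenever stoppers remit as often as completers. If stoppers remit more often than completers, the completer rate falls below 40%. The table describes a raw completer rate. It does not estimate bias in the planned mixed model.

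**The case against.** The strongest reply is that the session number in the Table 1 header is only the nominal end of an 18-session course. The Measures text calls T3 end-of-treatment without a session number, Primary outcomes calls it post-treatment, and the Therapist section places that role's "semi-structured interview after treatment delivery for each family". On this reading a family that stops early has its T3 when it stops. That reading is open, so a reader who infers that early stoppers can never reach T3 goes further than the text. The article does not choose between the two readings. If T3 is the actual end of treatment, follow-up length varies even more between families.

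A reader might also infer that effectiveness will come from completers alone. The documents do not support that. No completer-only set is defined, and a mixed model can keep families who have T1, T2 and session weights. Their T3 and T4 values would still be missing, and the estimate would rest on a missing-at-random assumption. How missing data are handled may be set out in a full protocol or SAP that is not shown, so its absence here is no finding.

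Three further inferences should be resisted:
- T3 is not the sole primary time point, because T1 to T4 is also a primary contrast.
- Upward bias is not established. Improving families may also end with fewer than 18 sessions, which would push the other way.
- Session 9 is a legitimate midpoint by dose. The article promises no calendar midpoint, and T2 is in neither primary contrast.

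Finally, feasibility does not depend on completers. Aim 2 counts families interested, enrolled, engaged and retained, and the therapist interview is held per family. Those counts show how many families left. The families' own account of why would still be missing.

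**Conclusion.** The point stands as a badly fixed anchor. Table 1 ties T2 and T3 to session counts in a study that expects some families to stop before session 18 and whose session pace follows response. On the literal reading, family and young-person acceptability data would come mainly from those who reach session 18. Both primary contrasts would lack T3 and T4 values for early stoppers and would mix follow-up lengths, and the mixed model mitigates this only in part. The loss is most certain for the surveys, the interviews and the Compulsive Exercise Test, which have no post-baseline collection before T3 in Table 1.

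Neither direction nor size of bias can be had from the document. The 40% to 57% range at 30% stopping rests on an assumed stopping share, assumed remission among stoppers and a true rate of 16 of 40. It would apply only if completers alone were counted, which the plan does not say.

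**What to change.** In Table 1 and the Measures text, define T3 and T4, and preferably T2, by time from T1 for every enrolled family regardless of sessions attended: for example T3 at 9 months and T4 six months later. Offer the evaluation survey and interview at the T3 date, or on stopping if that comes earlier. Use the same definition wherever T3 is called end-of-treatment or post-treatment. Sessions attended remain available as the engagement and retention indicators.

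This changes assessment timing only, not treatment. The cost is revised schedule wording, changed REDCap triggers and some effort to contact families who have stopped. It is best done early, because acceptability data missed when a family leaves may not be recoverable later.
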